### Description of study interventions and study procedures

**
Clinical assessment
**

Clinical assessment is conducted to confirm and ensure the participant is generally healthy.

•   
**Review of medical history:** The initial clinic visit will include a focused clinical history including obtaining information on any concurrent medical conditions, medications (including prescription, over the counter and illicit drug use) and vaccination history. Medical history may be confirmed with the GP records prior to the screen visit if there are any concerns or uncertainty remaining after the initial visit where eligibility has been assessed as indicated by the medical doctor.

•   
**Clinical examination:** The initial clinic visit will include a focused clinical history and targeted clinical examination including recording and evaluating vital signs including heart rate, blood pressure, temperature, oxygen saturations, auscultation of the lung fields and heart sounds. We will also measure weight and height, calculate BMI and estimate lean body mass.

Should a previously unrecognised abnormality be identified, this will be explained to the individual, and all relevant results will be forwarded to their GP so that appropriate investigations and follow-up can be arranged. Further participation will be determined at the discretion of the study doctor. If the participant has a positive HIV or hepatitis test, the result will be given by a suitably trained medical doctor and the participant will be referred to the local HIV/hepatitis service.

Participants may be re-screened at a later date to determine whether they meet eligibility criteria (e.g. if they have an acute infection on the date of screening that has subsequently resolved). They will be reimbursed for the additional study visit.

**
Clinical samples (obtained during study visits)
**

The following samples will be obtained during the study:

1.   
**Urine** – Participants will be asked to collect up to 20ml of urine at screening and vaccination visit for pregnancy testing (female).

2.   
**Nasopharyngeal and throat swab ± saliva** Nasopharyngeal and throat combined swab will be obtained during screening visits and prior to BCG challenge (using a rapid antigen test). The aim is to determine viral infection and recognise potential asymptomatic COVID-19 cases and protect the study participants and staff. IThe PCR tests will be performed in batch at study completion and will not be used to inform study procedures.

3.   
**Blood sampling** will be performed by trained, experienced staff. Blood volumes taken at each visit are based on the safety blood screening requirements and planned exploratory immunological investigations. The total clinical blood samples taken at each visit will be 50mls, which is a maximum of 350mls over the study.

4.   
**Punch biopsy** on the intradermal injection site will be performed according to routine dermatological procedures
^
20
^. Local anaesthetic injection will be required and one to two sutures to close the biopsy site. This procedure is planned to take place in both phase A (n=10 participants) and phase B (n=20 participants) and will be used as the gold standard comparator for minimally invasive skin sampling techniques. Written consent will be taken on the same day as the procedure. The procedure will be carried out by an appropriately trained doctor or nurse experienced in this procedure.

5.   
**Minimally invasive skin biopsy** on the intradermal injection site will be performed according to published procedures
^
17
^. This procedure is well tolerated by participants, does not require local anaesthetic; and does not leave a scar. Longitudinal sampling will be performed in Phase B with two microbiopsies taken at each time point (D0, D2, D7 and D14) circumferentially around the edge of the intradermal injection site taken at intervals described in
Table 1, avoiding previous biopsy sites.

6.   
**Skin scrape** on the intradermal injection site will be performed using a rhinoprobe (see nasal sampling) curette. Our group has established standardised operating procedures using this curette for nasal sampling
^
18
^. The procedure is minimally invasive and well tolerated by participants for nasal sampling. This will not be conducted in phase B.

7.   
**Skin swabs** will be rolled across the intradermal injection site at each subsequent study visit to determine if BCG can be accurately recovered and quantified using this technique. There are conflicting reports in the literature on this technique: Blazevic
*et al.*
^
21
^ demonstrated that paired classical and qPCR microbiological quantification techniques demonstrated significant kinetic association. However, another study was unable to culture BCG by swabbing of the injection site
^
13
^. In phase B this procedure will only be conducted if the injection site has ulcerated and there is concern about secondary infection.

8.   
**Nasosorption** will be obtained because we expect BCG to stimulate the respiratory mucosa. Sample strips are similar to blotting paper and developed by Hunts Development Ltd (UK). Strips collect concentrated nasal lining fluid before the nasal wash to measure inflammatory responses induced by infection that may be associated with increased colonisation density and acquisition. Concentrated nasal fluid will be used to measure cytokine levels by multiplex bead array. Blotting paper will be held inside the nostril for up to 3 minutes until soaked. These will then be removed and placed in a microcentrifuge tube for storage.

9.   
**Nasal wash will be obtained in a subset of participants only.** This will be performed using a modified Naclerio method. This is a well-used and validated technique to collect nasal bacterial specimens with which we now have 4 years’ experience. Briefly, 5ml of saline is instilled and held for a few seconds in the nares before being allowed to drip in to a sterile Galli pot; this is usually repeated up to 20ml in total. In the event of NW loss (defined as cough/sneeze/swallow) the procedure may then be repeated to obtain an adequate specimen.

10.   
**Nasal cells** will be collected after nasal wash using a nanosampling method in which cells are obtained through minimally invasive superficial nasal scrape biopsies (rhinoprobe) and participants can be biopsied multiple times with no significant side effects. Up to 4 samples will be obtained at each nasal sampling visit. If no cells are visible on the rhinoprobe following sampling, the sample can be repeated immediately.

**Symptom diary:** We will request that participants complete a symptoms diary for 14 days after intradermal injection. Participants will be asked to grade any symptoms from 0–4 on a Likert scale. This format has been previously utilised in our experimental human pneumococcal carriage studies. The results will be reviewed at visits D2 and D7. Participants will be advised to ensure the clinical team are contacted with any moderate to severe symptoms as soon as possible. Further details on clinical symptom scores and how these will be assessed are described in a specific section below.

**
Challenge visit (B)
**

*

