### Schedule of events and procedures

**Table 2. T2:** Schedule of visits and procedures. Visit 1 may occur up to four weeks before visit 2. X: event scheduled to occur throughout the study. A: event scheduled to occur only in Phase A. B: event scheduled to occur only in Phase B. *: Timeline is approximate only, as exact timings (± time windows) of visits relate to the actual (not intended) date of the previous visit. **in a selected subset of participants only. Phase A: punch biopsy is the gold standard comparator for BCG recovery
^
15
^ but is invasive, requiring local anaesthetic and a suture to close the wound. Our aim will be to validate less invasive techniques including minimally invasive skin biopsy
^
17
^ and a skin scrape
^
18
^ in the pilot phase (n=10) of the study. Phase B (n=20): we will select the optimal minimally invasive skin technique(s) from phase A and apply these longitudinally during study visits to assess BCG growth kinetics and interrogate immune responses over time. No local anaesthetic (LA) is required for minimally invasive biopsy; LA is known to cause artefactual blunting of humoral immune responses in laboratory assays. Nasal and throat swabs will be used to exclude SARS-CoV-2 infection prior to BCG challenge on day 0 (rapid antigen test) and subsequently to check for co-existent respiratory viral infection using PCR techniques. $ If screen >7 days from BCG. Β If virtual chat. Total blood volume per visit 50ml.

Study visit		1	2	3	4	5	6	7
Study day	Initial consent	Screening	Day 0	Day 2	Day 7	Day 14	Day 21	Day 28
Time windows (days) *				±1	±2	±2	±2	±5
Consent (Written)	x	xβ						
Consent (Verbal)	x	x	x	x	x	x	x	x
Eligibility check	x							
History and examination		x						
Vital Signs		x	x	x	x	x	x	x
Urine β-HCG		x	X$					
Screen for AEs			x	x	x	x	x	x
BCG challenge injection			x					
Skin punch biopsy						X		
Skin micro biopsy ^ 17 ^			B	B	B	x		
Skin scrape ^ 18 ^						A		
Skin swab			x	x	x	x	x	x
Inspect + photograph site			x	x	x	x	x	x
Stitch removal							X	
Diary card provided			x					
Diary card collected								x
FBC		x						
Coagulation		x						
PBMCs		x		x	x	x		
Serum			x	x	x	x		
HIV serology		x						
Blood RNA			x	x	x	x		
Nasosorption			B	B	B	B	B	B
Nasal wash **			B	B	B	B	B	B
Nasal scrape			B	B	B	B	B	B
Nasal & throat swab		B	B	B	B	B	B	B

**Table 3. T3:** Clinical assessment and STOP criteria.

Clinical history and examination	STOP if unexplained or concerning findings on history or examination

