•   Similar pattern of response to that seen to BCG intradermal injection, or

3 = Definite

•   Reasonable temporal relationship to BCG intradermal injection and

•   Event not readily produced by alternative aetiology (clinical, environment, or other interventions), and

•   Known pattern of response to BCG intradermal injection.

The chief investigator (CI), with the consultation of the trial steering committee (TSC), if required, will determine causality of AEs. The greatest degree of causal relationship (definite > probable > possible > unlikely related > not related) determined by either the PI or TSC after their discussions will determine the ultimate classification of the AE. Definite (4), probable (3) and possible (2) are considered to be related. No relationship (0) and unlikely (1) are unrelated.

**Table 5. T5:** Expected adverse events.

Expected adverse events
Pain/tenderness at the injection or biopsy site
Redness at the injection or biopsy site
Swelling at the injection or biopsy site
Warmth at the injection or biopsy site
Scaling/pustules at the injection or biopsy site
Transient ipsilateral axillary lymphadenopathy <1cm diameter
Scar at challenge (and biopsy site)
Headache
Fever (>38.3°C)

**
Procedure for recording adverse events
**

Participants will be asked to complete diary cards for 14 days after BCG challenge. They will be provided with a thermometer and tape measure to enable daily recording of temperature and local reactions at the injection site.

The diary cards will be reviewed at follow up visits and adverse events recorded in the CRF. Outside the diary card periods, expected local and systemic AEs (listed in
Table 5) will be specifically asked about and graded by severity (as detailed in
Table 6). Participants will be given the opportunity to report any other new symptoms since the last visit with start and stop dates and any treatments undergone.

All AEs (whether reported by the volunteer or solicited by the Investigator) will be clinically assessed at each visit and recorded in the CRF.

The following information will be recorded: description, date of onset and end date, severity and any treatment or intervention undertaken. The severity of events will be assessed on the following scale: 1 = mild, 2 = moderate, 3 = severe.

An assessment of relatedness to the BCG challenge will then be made by the Investigator.

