### Risk assessment

A risk assessment and monitoring plan will be prepared before the study opens and will be reviewed as necessary over the course of the study to reflect significant changes to the protocol or outcomes of monitoring activities. Specific risks are outline below.

**
Phlebotomy
**

The total amount of blood collected over the study period will be a maximum of 350mL. This amount should not compromise otherwise healthy participants. Risks occasionally associated with venepuncture include pain and bruising at the site of venepuncture, light-headedness, and syncope (rarely).

**
Nasal, nasopharyngeal and throat samples
**

This may cause some discomfort, eye watering or a small spot of blood. Participants may swallow the saline during nasal wash which may taste salty.

**
Challenge with BCG SSI
**

Full details are given in the summary of product characteristics (SmPC). In brief:

**
*Local reaction from intradermal BCG injection*
**

•   An inflammatory reaction as manifested by redness and swelling is expected to occur at the site of injection, followed by a local lesion that may ulcerate to be moist for up to three weeks. This heals over some weeks to months to leave a small flat scar. It is also possible to develop some swelling (<1cm diameter) of axillary lymph nodes.

•   Uncommonly (less than 1 in 100 people) swelling of axillary lymph nodes to more than 1cm across, or an ulcer that discharges fluid at the injection site may occur.

•   Rare side effects (less than 1 in 1000 people) include inflammation of lymph nodes leading to abscesses and discharge of fluid from the swellings.

**
*Systemic reactions*
**

•   Systemic reactions to BCG are rare (less than 1 in 1000 people) and include low-grade fever and headache, and allergic reactions. Disseminated complications of BCG, such as bone infections, have also been reported, but are extremely rare and have usually been reported in immunocompromised, not immunocompetent, individuals.

**
*Allergic reactions*
**

•   Allergic reactions from mild to severe may occur in response to any constituent of a medicinal product. Anaphylaxis is extremely rare but can occur.

**
Skin biopsy
**

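### Axillary nodes are split at 1 cm, but no axillary examination or node measurement is scheduled after challenge, so painless nodes may be under-recorded

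*Protocol article*

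**What the plan says.** **Classification.** Table 5 (Safety reporting) lists among the expected events "Transient ipsilateral axillary lymphadenopathy <1cm diameter". The Risk assessment section places "swelling of axillary lymph nodes to more than 1cm across" in a separate category, with a frequency below 1 in 100, and node abscesses in a rarer one.

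**Examination.** Under Description of study interventions and study procedures, the initial clinic visit includes a "targeted clinical examination including recording and evaluating vital signs including heart rate, blood pressure, temperature, oxygen saturations, auscultation of the lung fields and heart sounds". In Table 2 the row "History and examination" has one mark, at screening.

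**After challenge.** Table 2 schedules vital signs, "Screen for AEs" and "Inspect + photograph site" on Days 0, 2, 7, 14, 21 and 28. Participants keep a diary for 14 days. On their equipment, the article says: "They will be provided with a thermometer and tape measure to enable daily recording of temperature and local reactions at the injection site". Outside the diary period the Table 5 events "will be specifically asked about and graded by severity". Adverse events that are reported or solicited are clinically assessed at each visit.

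**Grading.** Table 6 gives millimetre bands for redness and swelling at the injection or biopsy site and temperature bands for fever. It has no row for nodes, so they fall into the residual category, which is graded by symptoms and interference with activity.

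**STOP check.** The Participant identification section says eligibility is confirmed at screening and at follow-up visits, and one STOP criterion in Table 3 refers to findings on history or examination.

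**The concern.** Regional lymphadenopathy is a reaction to BCG that the article itself names, and the challenge dose is three times the routine one. Safety and tolerability are a stated objective and a secondary endpoint. The article defines the lymphadenopathy term by diameter and by transience. Diameter needs a measurement and transience needs at least two, and telling a new node from an old one needs a baseline. None of these is scheduled.

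An event collected mainly by report will tend to be under-counted when it is often painless. In a study of 30 people, missing one or two nodes changes the reported incidence materially. The class also has a use: the article requires adverse events that are unexpected, likely related and persisting at the end of the study to be followed to resolution.

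**Working it through.** The article gives no incidence, detection rate or precision target for lymphadenopathy, so there is no figure to reproduce. The check has two parts.

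**1. What the definition needs, against what is collected**

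- *Node diameter against 1 cm (Table 5, Risk assessment).* The participant's tape measure is for the injection site. Site inspection in Table 2 names the site, not the axilla. Table 6 asks for no node diameter.
- *Transience (Table 5).* No repeated node measurement is scheduled.
- *Baseline.* Table 2 has one examination, at screening. Its described content does not name the axilla. The list opens with 'including', so palpation is neither stated nor ruled out.
- *Detection of a node the participant has not noticed.* In the first 14 days the stated routes are the diary, its review at visits and the adverse event screen. After that, listed events are specifically asked about. All of these start from the participant's own awareness. Clinical assessment applies to events already reported or solicited. In Table 6 the residual category gives grade 0 when there is no symptom, so a painless, unnoticed node would grade as nothing.
- *Repeat examination.* The text confirms eligibility at follow-up, and Table 3 has a criterion based on examination findings, but Table 2 marks the eligibility check at initial consent and the examination at screening only. These places do not agree.

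**2. Illustration of what incomplete detection would do**

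Inputs: n = 10 (Phase A) + 20 (Phase B) = 30. True rate p: 1%, the article's upper bound for nodes over 1 cm, and 10%, assumed. Detection probability s: assumed, because the article gives none.

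Expected recorded cases = n·p·s. Chance of recording at least one = 1 − (1 − p·s)^30.

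| p | s | Expected recorded | P(at least one) |
|---|---|---|---|
| 1% | 1 | 0.30 | 26.0% |
| 1% | 0.75 | 0.225 | 20.2% |
| 1% | 0.5 | 0.15 | 14.0% |
| 1% | 0.25 | 0.075 | 7.2% |
| 10% | 1 | 3.0 | 95.8% |
| 10% | 0.75 | 2.25 | 90.4% |
| 10% | 0.5 | 1.5 | 78.5% |
| 10% | 0.25 | 0.75 | 53.2% |

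If no case is recorded in 30, the one-sided 95% upper limit on the recorded rate is 1 − 0.05^(1/30) = 9.5%. The corresponding limit on the true rate is 9.5%/s: 11.9% at s = 0.8, 19.0% at s = 0.5 and 31.7% at s = 0.3.

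Missed nodes can only lower the count, so the direction is clear. The amount depends entirely on s.

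**The case against.** The strongest reply is that this is a condensed article. Which regions are palpated is ordinary content of a site procedure or case report form, and the article says approved site-specific procedures will be used. The described examination is an open list for the initial visit, meant to confirm general health, so its silence on the axilla says little about follow-up. This stands as a caution: the full protocol may specify palpation. It does not remove the point, because Table 2 is a visit-by-visit schedule and the route that the article does state is triggered by reports.

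A reader might infer that a node is found only if the participant notices it. The documents do not support that. Lymphadenopathy is a listed event that staff ask about, reported or solicited events are clinically assessed at each visit, and the text rechecks STOP criteria at follow-up.

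A reader might also infer that the safety result as a whole is biased low, or that the decision to enter Phase B is affected. Neither follows. The gap concerns one event term. The safety criteria for progression are tolerated procedures and no challenge-related SAE or SUSAR, and an unnoticed, non-serious node bears on neither. Expectedness is also determined from the product characteristics, so Table 5 is not the only classifier.

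Finally, the detection rates are assumptions. At the article's own ceiling of 1% for nodes over 1 cm, most studies of 30 would record none even with full detection (100% − 26.0% = 74.0%). The likely misses are small nodes that the article already expects. That limits the importance of the point.

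**Conclusion.** The point holds for the lymphadenopathy term. The article separates axillary nodes at 1 cm, but the post-challenge procedures it states include no axillary examination and no node measurement, and no axillary baseline is stated. Recording therefore depends mainly on the participant noticing or reporting a node. Painless nodes may be under-recorded, and the split at 1 cm may rest on no planned measurement.

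The size of any under-count cannot be derived from the document. The figures above show only how an assumed detection rate would carry through. The conclusion assumes that no document outside the article already prescribes axillary palpation at these visits. If one does, Table 2 should show it. This is an inexpensive improvement to ascertainment, not a flaw that threatens the study's main conclusions.

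**What to change.** 1. Extend the Table 2 row "Inspect + photograph site" to include palpation of the ipsilateral axilla before injection on Day 0 and at each follow-up visit. Enter the largest node diameter, or 'none felt', in the eCRF.
2. Classify nodes against the 1 cm limit from that measurement, with the Day 0 finding as baseline.
3. Report nodes found on examination separately from nodes volunteered by participants, so that the result can still be compared with studies that relied on reports.
4. Reconcile Table 2 with the Participant identification section and Table 3 on whether examination is repeated at follow-up.

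**Cost.** Staff already inspect the same arm at these visits, so no visit or sample is added. At an assumed one minute each, 30 participants × 6 visits = 180 examinations, or about 3 hours over the study, plus one eCRF field. The downside is that more small, benign nodes will be recorded and the adverse event count will look slightly less favourable. Separate reporting of examined and volunteered nodes makes that visible.

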## Abstract

Tuberculosis (TB) caused 1.5 million deaths in 2020, making it the leading infectious killer after COVID-19. Bacille Calmette-Guerin (BCG) is the only licensed vaccine against TB but has sub-optimal efficacy against pulmonary TB and reduced effectiveness in regions close to the equator with high burden. Efforts to find novel vaccines are hampered due to the need for large-scale, prolonged, and costly clinical trials. Controlled human infection models (CHIMs) for TB may be used to accelerate vaccine development by ensuring only the most promising vaccine candidates are selected for phase 3 trials, but it is not currently possible to give participants
*Mycobacterium tuberculosis* as a challenge agent.

This study aims to replicate and refine an established BCG CHIM at the Liverpool School of Tropical Medicine. Participants will receive an intradermal injection with licensed BCG vaccine (Statens Serum Institut strain). In phase A, participants will undergo punch biopsy two weeks after administration, paired with minimally invasive methods of skin sampling (skin swab, microbiopsy, skin scrape). BCG detection by classical culture and molecular methods will be compared between these techniques and gold standard punch biopsy. Techniques meeting our pre-defined sensitivity and specificity criteria will be applied in Phase B to longitudinally assess intradermal BCG growth two, seven and fourteen days after administration. We will also measure compartmental immune responses in skin, blood and respiratory mucosa in Phase B.

This feasibility study will transfer and refine an existing and safe model of BCG controlled human infection. Longitudinal BCG quantification has the potential to increase model sensitivity to detect vaccine and therapeutic responses. If successful, we aim to transfer the model to Malawi in future studies, a setting with endemic TB disease, to accelerate development of vaccines and therapeutics relevant for underserved populations who stand to benefit the most.

**Registration:** ISRCTN:
ISRCTN94098600 and ClinicalTrials.gov:
NCT05820594

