## Protocol

### Objectives and outcome measures

**
Overarching aim
**

To establish the safety and feasibility of an established BCG controlled human infection model in Liverpool, UK.

**
Specific objectives (
Table 1)
**

1.   Confirm microbiological and molecular recovery of BCG at the intradermal injection site by gold standard skin punch biopsy (punch biopsy) 14 days after challenge

2.   Confirm safety and tolerability in healthy adult participants

3.   Determine agreement between less invasive skin biopsy techniques (including swabs, skin scrapes and microbiopsy) compared to gold standard punch biopsy on microbiological and molecular recovery of BCG with an aim to employ less invasive methods within a refined protocol in future.

4.   Confirm optimal procedures to assess immune response to BCG intradermal challenge locally (skin tissue), systemically (blood) and in the respiratory mucosa (nasal samples).

**Table 1. T1:** Outcome measures: Objectives and endpoints.

	Objectives	Endpoints
**Primary**	To quantify BCG recovered from the intradermal BCG challenge site 14 days after injection	Culture and PCR quantification of BCG at intradermal challenge site by punch biopsy
**Secondary**	Confirm safety and tolerability of study procedures in participants	Actively (solicited) and passively collected data on adverse events
	Confirm agreement between BCG recovery between punch biopsy and minimally invasive skin biopsy	Pairwise comparison between culture and PCR quantification by punch and micro skin biopsy
	Confirm agreement between BCG recovery between punch biopsy and minimally invasive skin scrape	Pairwise comparison between culture and PCR quantification by punch biopsy and skin scrape
	Longitudinal quantification of BCG recovery from the intradermal BCG challenge site at 2, 7, 14, 21 and 28 days	Culture and PCR quantification of BCG at intradermal challenge site by non-invasive skin swab.
	Confirm laboratory assays for immune response to BCG at intradermal injection site	Skin biopsy cell pellet(s) examined for immune cell differentiation and antigen stimulation
	Confirm laboratory assays for immune response to BCG in systemic circulation	Immune cell activation and functional assays; and cytokine levels in blood
	Measure immune response to BCG injection in respiratory mucosa	Nasal scrape pellet and nasal lining fluid examined for cell differentiation and activation and cytokine expression

**
Study hypotheses
**

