### Expenses and benefits

It is not intended that financial factors influence an individual's decision to participate in this study. The fees will reflect remuneration and not financial coercion. We compensate participants for time, travel, inconvenience and discomfort. The sums offered in this study have been developed over the course of many years for pneumonococcal controlled human infection studies and are consistent with remuneration in other similar local and national studies and are detailed below (
Table 7). 

**Table 7. T7:** Payment summary. The screen and vaccination appointment can be performed as a separate visit or combined as required, the remuneration will be unchanged. Participants will be provided remuneration by direct bank transfer following attendance at visit 7. Remuneration is pro-rata based on the number of visits attended and samples taken. If a participant withdraws from the study early, they will be remunerated for the visits they attended and samples which were taken up until the time they withdrew. If additional visits are required, the participant will be reimbursed for that visit.

Phase A								
	Visit 1	Visit 2	Visit 3	Visit 4	Visit 5	Visit 6	Visit 7	
Samples taken	Screening	Day 0	Day 2	Day 7	Day 14	Day 21	Day 28	
Urine	X	X						
BCG Challenge		X						
Skin punch biopsy					X			
Skin micro biopsy					X			
Skin scrape					X			
Skin swab		X	X	X	X	X	X	
Bloods	X	X	X	X	X	X	X	
Nasosorption								
Nasal cells								
Nose and throat swab	X	X	X	X	X	X	X	
Time taken	60	60	20	20	90	20	20	TOTAL
Remuneration	£40	£50	£20	£20	£150	£20	£20	£320
Phase B								
	Visit 1	Visit 2	Visit 3	Visit 4	Visit 5	Visit 6	Visit 7	
Samples taken	Screening	Day 0	Day 2	Day 7	Day 14	Day 21	Day 28	
Urine	X	X						
BCG Challenge		X						
Skin punch biopsy					X			
Skin micro biopsy		X	X	X	X			
Skin swab		X	X	X	X	X	X	
Bloods	X	X	X	X	X	X	X	
Nasosorption	X	X	X	X	X	X	X	
Nasal cells	X	X	X	X	X	X	X	
Nose and throat swab	X	X	X	X	X	X	X	
Time taken	60	60	60	60	90	60	60	TOTAL
Remuneration	£40	£55	£55	£55	£150	£55	£55	£465

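### The skin-swab endpoint for longitudinal BCG recovery has contradictory sampling rules, and its day-21 and day-28 swabs are not comparable with earlier ones once a punch biopsy has been taken

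*Protocol article*

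**What the plan says.** Table 1 (Objectives and outcome measures) lists as a secondary objective "Longitudinal quantification of BCG recovery from the intradermal BCG challenge site at 2, 7, 14, 21 and 28 days". The endpoint beside it is "Culture and PCR quantification of BCG at intradermal challenge site by non-invasive skin swab". No other sampling method is named in that row, and the row is not restricted to a phase.

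The schedules agree with Table 1. Table 2 marks the swab row with x on days 0, 2, 7, 14, 21 and 28, and its legend reads "X: event scheduled to occur throughout the study". Table 7 marks Phase B swabs at all six visits from day 0 to day 28, and its note says "Remuneration is pro-rata based on the number of visits attended and samples taken".

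The swab item under Description of study interventions and study procedures says two things. It opens by stating that swabs "will be rolled across the intradermal injection site at each subsequent study visit to determine if BCG can be accurately recovered". It closes, for Phase B, with "In phase B this procedure will only be conducted if the injection site has ulcerated and there is concern about secondary infection".

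The Abstract, by contrast, says that techniques passing Phase A will be used in Phase B to "longitudinally assess intradermal BCG growth two, seven and fourteen days after administration". The Phase B text under Study design likewise assigns growth kinetics to the technique or techniques chosen in Phase A. The microbiopsy item schedules two Phase B microbiopsies at each of days 0, 2, 7 and 14.

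The punch is taken from the injection site at day 14. The punch item says "Local anaesthetic injection will be required and one to two sutures to close the biopsy site", and Table 2 places stitch removal at day 21. Table 2, the punch item and Table 7 include a Phase B punch. The Phase B text under Study design describes the single punch as being replaced by longitudinal minimally invasive sampling.

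**The concern.** There are two separate problems with one named secondary endpoint.

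The first is who is swabbed. Staff who follow Table 2 and staff who follow the closing sentence of the swab item would collect different Phase B data. Swabs taken only because a site has ulcerated and looks infected are a clinically triggered sample, not a kinetic series. The Risk assessment section describes a lesion that may ulcerate and stay moist, and notes that low levels of BCG can be found by swabbing the moist surface. The trigger is therefore plausibly related to the quantity being measured.

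The second is what is swabbed. After a punch, the day-21 and day-28 swabs come from a site from which tissue has been removed. Table 1 treats all five days as one series and makes no allowance for this.

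The Abstract presents longitudinal quantification as the route to a more sensitive model. The reader should be able to tell which series is meant, in whom, and from what kind of site.

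**Working it through.** No power, margin or calculated sample size is attached to this endpoint, so there is no stated figure to reproduce. The check is a count of scheduled swabs under each reading.

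Inputs: Phase A n = 10 and Phase B n = 20 (Study design); five post-challenge days, 2, 7, 14, 21 and 28 (Table 1); punch at day 14 (Table 2). The full schedule is 30 × 5 = 150 swabs.

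| Reading | Scheduled swabs | Days 2–14 | Days 21/28 after a punch | Days 21/28, no punch |
|---|---|---|---|---|
| (a) Phase B limit in the swab item governs | 10 × 5 = 50 | 10 × 3 = 30 | 10 × 2 = 20 | 0 |
| (b) Tables 2 and 7 govern; punch in both phases | 30 × 5 = 150 | 30 × 3 = 90 | 30 × 2 = 60 | 0 |
| (c) Tables 2 and 7 govern for swabs; no Phase B punch | 30 × 5 = 150 | 30 × 3 = 90 | 10 × 2 = 20 | 20 × 2 = 40 |

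- **Reading (a).** Scheduled swabs are 50/150 = 33% of the full schedule, and those on days 2–14 are 30/150 = 20%. Phase B adds an unknown, lesion-selected number between 0 and 20 × 5 = 100.
- **Reading (b).** 60/150 = 40% of swabs follow a punch.
- **Reading (c).** 20/150 = 13% follow a punch.
- **Complete series.** The number of participants with an unselected day 2–28 series from an unpunched site is 0 under (a), 0 under (b) and 20 under (c).
- **Precision.** With 10 participants instead of 30, the standard error at each time point is √(30/10) = √3 = 1.73 times as large, if the variance is the same.

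The day 2–14 counts treat the day-14 swab as taken before the punch. The Phase A text says only that the paired samples are taken in parallel with the punch and after local anaesthetic. It does not fix the order.

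The kinetic plan also differs from one place to another:

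- Table 1, longitudinal row: swab; days 2 to 28; no phase stated.
- Abstract: technique(s) passing Phase A; days 2, 7 and 14; Phase B.
- Microbiopsy item: microbiopsy; days 0, 2, 7 and 14; Phase B.

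Table 1 has no row for longitudinal BCG recovery by microbiopsy. Its one longitudinal recovery row uses the method that the swab item withdraws from routine use in Phase B.

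**The case against.** The strongest reply is that little is lost. Even if the Phase B limit governs, all 10 Phase A participants have unconditional swabs on all five days, with days 2, 7 and 14 falling before or at the punch visit, and Table 1 does not say that the endpoint needs all 30. The wider kinetic aim survives through the Phase B microbiopsies. The primary endpoint is the day-14 punch, and the recovery criteria for moving to Phase B use day-14 samples only. The study is a feasibility study not sized for significance. Nowhere does the protocol say that Phase A and Phase B swabs will be pooled.

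All of that stands, and it limits how far the point can be taken. Three stronger readings are tempting, but the documents do not support them:

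- **That the endpoint cannot be delivered.** Phase A still delivers part of it, and reading (c) gives a complete series in 20 participants. However, (c) requires setting aside the Phase B swab limit and also the Phase B punch shown in Table 2, Table 7 and the punch item.
- **That the post-punch swabs are worthless, or that a false clearance of BCG will appear.** Neither the punch size nor whether the whole lesion is removed is given, and a wound could move surface recovery in either direction. Stitches are due out at day 21, so by day 28 the site is biopsied but no longer expected to be sutured. Lack of comparability is all that can be claimed.
- **That selection inflates swab recovery by some stated amount.** The protocol gives no frequency for the joint trigger of ulceration and concern about infection, and no positivity by lesion state. The Risk assessment puts a discharging ulcer below 1 in 100, which is not the same event.

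The reply does not remove the contradiction between the swab item and Tables 1, 2 and 7. Nor does it make a swab of a biopsied site comparable with one of an intact site.

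**Conclusion.** The point holds as a contradiction and a comparability problem. The closing sentence of the swab item conflicts with Tables 1, 2 and 7 and with its own opening sentence. Depending on which text governs, the endpoint rests on 50 or on 150 scheduled swabs. Where a punch is taken, two of the five time points (40%) come from a biopsied site. That applies to all 10 Phase A participants, and to all 30 if Table 2, Table 7 and the punch item govern for Phase B. A change after day 14 in those participants cannot be attributed to BCG growth or decline.

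These counts assume full recruitment, no missed visits, and a day-14 swab taken before the punch. The size and direction of the biopsy effect, and of any selection effect in Phase B, cannot be derived from the protocol.

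This should be corrected, but it does not threaten the trial's main conclusion. The endpoint is secondary, and no stated progression decision uses a day-21 or day-28 swab.

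**What to change.** 1. Reconcile the Phase B sentence of the swab item with its opening sentence and with Tables 1, 2 and 7. Reconcile the Phase B text under Study design with Table 2, Table 7 and the punch item on whether Phase B has a punch. Which text should govern is for the investigators to settle.
2. Restate the Table 1 longitudinal endpoint by phase, technique and day. For Phase A: swabs at days 2, 7 and 14, with the day-14 swab taken before the punch. For Phase B: the technique or techniques carried forward from Phase A, on the days when they are sampled.
3. For anyone who had a punch, leave day-21 and day-28 swabs out of the kinetic series and report them separately. Keep them in the series only for participants with an unpunched site and unconditional swabs, so that the 20 Phase B series under reading (c) are not discarded if that reading is confirmed.
4. State that ulcer-triggered Phase B swabs will not be combined with scheduled swabs.

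The cost is fewer claimed swab time points (three rather than five wherever a punch is taken) and a protocol amendment with the approvals that go with it, including changes to the schedule and payment tables. No extra sampling is needed. The Study status section says that recruitment had not begun at submission; if that is still so, the change can be made before any data exist.
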